Patients will be excluded if they fail to attend scheduled telerehabilitation sessions or respond to WhatsApp communication. Those experiencing unexpected medical complications, such as infections or cardiac or respiratory events, will be instructed to discontinue the program and withdraw from the study. The exclusion criteria also included changes in clinical status leading to surgical contraindications or new injuries during the prehabilitation period that prevented participation in home exercises. Additionally, participants with cognitive deficits were excluded based on the Portuguese version of the Mini-Mental State Examination (MMSE), with cut-off scores of ≤20 for illiterate individuals, ≤25 for primary school level, ≤26.5 for junior high school, ≤28 for high school, and ≤29 for higher education [15].

Randomization

After the explanatory meeting, eligible participants who complete baseline assessments will be randomized using simple randomization with a 1:1 allocation ratio via Randomizer® (www.randomizer.org). The allocation sequence will be generated by an independent researcher not involved in enrollment or assessment. Allocation concealment will be ensured using sequentially numbered, opaque, sealed envelopes, which will be opened only after confirming participant eligibility.

Control group

The participants in the control group will receive an institutional educational booklet containing standard preoperative physiotherapy recommendations. The only exercise instructions before TKA provided in the booklet were as follows: “(1) Move your feet up and down 20 times (active movement while lying on a treatment table, plantar dorsiflexion) and (2) inhale deeply through your nose while raising your arms and exhale through your mouth as you lower them. Perform 20 repetitions.” Participants in the control group will only follow these institutional procedures and will not engage in a home-based program. They will be instructed to maintain their usual daily activities and adhere to the recommendations provided in the booklet.

Experimental group

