In TKA, the extent of surgical trauma significantly influences postoperative pain and recovery. Plasma CRP, a well-established biomarker of tissue injury and inflammation, is commonly used to monitor recovery due to its rapid response, high specificity for acute inflammation, and ease of measurement, especially in elderly arthroplasty patients. CRP was selected as the primary outcome because of its association with osteoarthritis severity, surgical response, and postoperative complications, typically peaking on the third postoperative day [17].

Blood samples will be collected in an outpatient setting at four periods: before and after the eight-week prehabilitation program and three and 30 days post-TKA in both the experimental and control groups. The preoperative measurement one day before surgery (t3 in Figure 1) was timed to reflect chronic systemic adaptations resulting from prehabilitation while minimizing the confounding influence of acute exercise responses. This decision is supported by evidence showing that CRP typically returns to baseline (or a new post-exercise baseline) within six days after cessation of exercise [18]. The third postoperative day (t5) was selected to capture the peak inflammatory response following surgery, as supported by TKA-specific literature [17]. This time point also coincides with the typical hospitalization period, facilitating consistent, in-hospital sample collection. In the long term, given the anti-inflammatory effects of physical exercise, sustained reductions in CRP levels may reflect the effectiveness of the intervention in modulating systemic inflammation and promoting recovery [14].

Given that CRP levels can be influenced by factors such as sleep deprivation and acute infections, additional control measures will be implemented. Participants will report their average sleep duration and quality during the week preceding each blood draw (except for the third-day post-TKA measurement), as insufficient or disturbed sleep is associated with elevated CRP levels. Additionally, clinical symptoms suggestive of viral or bacterial infections (e.g., fever, sore throat, cough, or malaise) will be assessed before each collection since such conditions may increase CRP levels and confound the interpretation of the intervention's effects [19]. These precautions aimed to strengthen the internal validity of CRP as a primary outcome by minimizing interference from unrelated acute inflammatory processes.

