Patient satisfaction will be assessed 30 days post-TKA using a validated TKA satisfaction questionnaire [27]. This time point was selected to capture the short-term functional and symptomatic benefits of prehabilitation when effects on recovery are most tangible. Four primary questions, rated on a five-point Likert scale, will evaluate pain relief, functional improvement, and overall satisfaction. Scores ranged from 0 (very dissatisfied) to 100 (very satisfied), with the total score calculated as the mean of all responses. The total satisfaction score will be obtained by summing the individual scores of the four satisfaction questions and dividing by four. If any individual component is missing, the total score will not be calculated.

Sample size

The sample size was estimated using repeated measures analysis of variance with four time points (nine weeks pre-TKA, one day pre-TKA, three days post-TKA, and 30 days post-TKA) and two groups (experimental and control). Assuming a moderate effect size (f = 0.25), α = 0.05, and 80% power (β = 0.20), 78 participants were required (G*Power 3.1.9.7, University of Kiel, Germany). This effect size was selected based on evidence from a study in TKA patients with CRP as the primary outcome, which reported a between-group difference of 9.12 mg/L and a pooled standard deviation of 10.95, corresponding to a Cohen’s d of 0.83 (f ≈ 0.29), and statistical power of 88% with 61 participants. Therefore, f = 0.25 was adopted as a conservative and evidence-based estimate for the current trial [28]. Accounting for a 10% potential attrition rate, the final target sample size was 86 participants.

Blinding

This study follows a single-blind design, in which only the data analyst remains blinded to group allocation. Due to the nature of the intervention (an exercise program), blinding participants or intervention providers was not feasible, as doing so would compromise adherence, safety, and protocol fidelity. Consequently, participants, data collectors, and outcome assessors will be aware of group assignments.

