## Results

The significance level was set at p < 0.05, and analyses will be performed using IBM SPSS Statistics 21.0 (IBM®, Armonk, NY, USA). Data normality will be assessed using the Shapiro-Wilk test. Baseline demographic characteristics will be compared between the groups using independent t-tests (normal data), Mann-Whitney U tests (non-normal data), and chi-square or Fisher’s exact tests (categorical variables).

The primary outcome, changes in plasma CRP levels across four time points (nine weeks pre-TKA, one day pre-TKA, three days post-TKA, and 30 days post-TKA), and WOMAC scores across three time points (baseline, one day pre-TKA, and 30 days post-TKA) will be analyzed using two-way repeated-measures ANOVA (group × time interaction), contingent upon assumptions of normality and sphericity. If these assumptions are violated, linear mixed models (LMM) or generalized estimating equations (GEE) will be employed as more robust alternatives, capable of handling missing data and irregular intervals. Post-hoc pairwise comparisons will use the Bonferroni correction to adjust for type I errors. For non-parametric repeated measures, the Friedman test will be used, followed by Dunn-Bonferroni post-hoc tests when applicable.

Secondary outcomes, including synovial fluid and tissue biomarkers, hospital outcomes (length of stay, complications, readmissions), and satisfaction scores at specific time points, will be compared between groups using independent t-tests (normal data) or Mann-Whitney U tests (non-normal data). Correlations between biomarkers, hospital outcomes, WOMAC scores, and satisfaction will be examined using repeated measures correlation (rmcorr) for normal data or generalized linear mixed model (GLMM) for non-normal data. Rmcorr will be applied when assessing the strength and direction of associations between two continuous variables measured repeatedly within individuals. GLMM will be used in cases requiring the modeling of random effects, adjustment for covariates, or handling of non-normal or categorical outcomes, ensuring analytic flexibility across diverse data structures. To account for multiple comparisons in biomarker and exploratory analyses, false discovery rate (FDR) adjustment will be applied where appropriate.

Effect sizes (e.g., partial eta-squared for ANOVA and Cohen’s d for pairwise tests) and 95% confidence intervals will be reported alongside p-values to enhance the clinical interpretability of findings.

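### Assumption checks choose the primary CRP method and no scale is fixed: the planned RM-ANOVA would rarely be run, and its fallbacks on mg/L are invalid for the question or lose power

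*Protocol article*

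**What the plan says.** The statistical paragraphs of the Results section make the primary analysis a two-way repeated-measures ANOVA of plasma CRP at nine weeks and one day before surgery and at 3 and 30 days after it. The term of interest is group × time, and the model applies only if normality and sphericity hold. The text continues: "If these assumptions are violated, linear mixed models (LMM) or generalized estimating equations (GEE) will be employed as more robust alternatives". Bonferroni pairwise comparisons follow, and the Friedman test with Dunn-Bonferroni comparisons is given for the non-parametric case. Nothing says whether LMM or GEE is to be used, and no transformation is named.

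The visits have different purposes (Materials and methods, Primary outcome). The pre-operative sample "was timed to reflect chronic systemic adaptations resulting from prehabilitation". The day-3 sample "was selected to capture the peak inflammatory response following surgery".

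The Sample size section is built on "repeated measures analysis of variance with four time points": "Assuming a moderate effect size (f = 0.25), α = 0.05, and 80% power (β = 0.20), 78 participants were required". The study behind the effect size "reported a between-group difference of 9.12 mg/L and a pooled standard deviation of 10.95", so the sizing is on the mg/L scale. The visit to which those figures belong is not stated.

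**The concern.** Three features of the stated rule work against each other.

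- **The method depends on the data.** Four procedures are listed, the choice among them rests on tests of the trial's own data, and no rule separates LMM from GEE.
- **The fallbacks do not all answer the failed assumption.** An LMM assumes normal residuals as the ANOVA does, so on mg/L it leaves skewness untouched. It can deal with failed sphericity, but only if its covariance allows a different variance at each visit, and that is not fixed. Friedman is a one-sample within-patient test with no group × time term, so it cannot test the primary hypothesis.
- **The scale matters.** One visit was chosen for its extreme values. In mg/L its spread can dominate any error term pooled over visits, including the comparison at the visit placed to show what eight weeks of exercise did.

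At stake is which primary test the trial reports, and how much chance that test has of seeing a pre-operative effect.

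**Working it through.** **1. The plan's own figure.** G*Power's between-group test has λ = f²·N·m / (1 + (m−1)ρ). With f = 0.25, N = 78, m = 4 and an assumed ρ = 0.5, λ = 0.0625 × 78 × 4 / 2.5 = 7.8. Power is 78.7%, and 82 would be needed. For the group × time term, λ = f²·N·m·ε / (1−ρ). With ρ = 0.5 and ε = 1, 24 patients suffice (λ = 0.0625 × 24 × 4 / 0.5 = 12). So 78 is not reproduced with default settings. That is a separate matter. Here it supplies a yardstick: λ of about 12 gives 80% power for the interaction.

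**2. Assumed CRP values.** The documents give none by visit. The simulations took log-normal CRP, 39 per arm, with medians of 3–5 mg/L at baseline and pre-operatively, 60–150 at day 3 and 6–10 at day 30. Log-SDs were 0.4–1.1 and correlations 0.3–0.7.

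**3. One setting by hand.** Medians 4/4/100/8, log-SD s = 0.9 (0.5 at day 3), ρ = 0.6.
- SD = median × exp(s²/2) × √(exp(s²) − 1), giving 6.7, 6.7, 60.4 and 13.4 mg/L.
- Day-3 share of variance: 60.4² / (6.7² + 6.7² + 60.4² + 13.4²) ≈ 0.93. Over the range of one set of settings it is 80–98%.
- ANOVA interaction error = mean variance − mean covariance. With covariance = meanᵢ·meanⱼ·(exp(ρsᵢsⱼ) − 1), this is 979 − 159 = 820.
- A 35% fall at the pre-operative visit only is 0.35 × 6.0 = 2.10 mg/L. Interaction sum of squares = (39/2) × 2.10² × (1 − 1/4) = 64.5, so λ = 64.5 / 820 ≈ 0.08.
- The same fall in logs is ln(0.65) = −0.431. Sum of squares = 19.5 × 0.186 × 0.75 = 2.71; error = 0.670 − 0.378 = 0.292; λ ≈ 9.3.

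The mg/L ANOVA has almost no signal for this effect. A random-intercept LMM on balanced data gives the same F.

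**4. Which branch is reached?** In four settings of this kind, Mauchly's test rejected sphericity in 100% of runs, with ε of 0.34–0.36 (the minimum for four visits is 1/3). Shapiro-Wilk at n = 39 rejects log-normal data in 84%, 98% and 99.8% of samples at log-SD 0.5, 0.7 and 0.9. Even with exactly normal CRP, eight independent checks (arm by visit, a layout the plan does not state) would reject at least once with probability 1 − 0.95⁸ = 0.337.

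**5. Simulated power.** Rows come from separate runs with different assumed values, so compare across a row, not down a column. GG is the Greenhouse-Geisser correction.

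| Analysis | CRP effect | mg/L | ln(CRP) |
|---|---|---|---|
| RM-ANOVA, GG | pre-op −30% | 4–6% | 32–90% |
| RM-ANOVA, GG | pre-op −50% | 4–7% | 87–100% |
| RM-ANOVA, GG | pre-op and day 30, −35% | 5–6% | 68–97% |
| RM-ANOVA, GG | day 3 only, −20% | 46–74% | 12–49% |
| RM-ANOVA, GG | all later visits, −30% | 80–97% | 30–89% |
| Joint test of changes, visit-specific variances | pre-op −30% | 12–50% | 30–87% |
| Joint test of changes, visit-specific variances | pre-op −50% | 29–95% | 87–100% |
| Joint test, baseline as covariate | pre-op −35% | 31–72% | 57–82% |
| Joint test, baseline as covariate | day 3 only | 35–91% | 44–97% |
| Joint test, baseline as covariate | equal at all later visits | 84–97% | 91–99% |

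**The case against.** A reader might infer that the primary test is nearly blind to a pre-operative effect. The documents do not support that. The ANOVA is conditional on sphericity, and the day-3 peak that ruins its power also makes sphericity fail, so the plan moves to LMM or GEE. With visit-specific variances or robust standard errors, power on mg/L is weak in places but not near alpha. The blindness belongs to the ANOVA, or to a random-intercept LMM, which the text neither specifies nor excludes.

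Two other strong readings also fail. The remedy is not only a mixed model: GEE is offered and needs no normal residuals. Nor is it certain that a pre-operative benefit would go unreported. A Bonferroni comparison (α/3) of the mg/L change at the pre-operative visit has 9–46% power for a 30% fall and 28–93% for 50%.

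It is also fair that mg/L can be the stronger scale. In the ANOVA it wins when the effect is at day 3 or equal at all later visits. The same holds, for equal effects, in a joint test of unadjusted changes from baseline (about 73–99% against 30–89%). The advantage disappeared once baseline was a covariate, so the covariate is an essential part of the fix.

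Every magnitude is assumed. The only SD in the document is 10.95 mg/L, at no stated visit, against 27–91 assumed at day 3. Were 10.95 the day-3 SD, with SDs of 4.0, 3.9 and 6.3 elsewhere, the day-3 share would be 119.9 / (119.9 + 16.0 + 15.2 + 39.7) = 63%. Day 3 would dominate less.

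Finally, an unstated transformation or covariance structure could sit in an analysis plan that is not shown, and that silence alone is no finding. What stands is that the article itself states the model, the trigger and the fallbacks, and the rule as stated is faulty.

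**Conclusion.** The concern holds as a fault in the stated rule. The primary CRP method is chosen by assumption tests, the ANOVA used for sizing would rarely survive them, and the listed replacements are of unequal worth. Friedman cannot test the hypothesis. An LMM on mg/L does not cure skewness, and with only a random intercept it keeps the ANOVA's power near alpha for effects limited to the pre-operative visit or to the pre-operative and day-30 visits. GEE, or an LMM with visit-specific variances, is usable but gives up power on mg/L.

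The direction rests on the documents' own statement that CRP peaks around day 3. The percentages rest on log-normal CRP with a day-3 SD far above that of the other visits. The weakness concerns effects outside day 3, and nothing here shows that the trial as a whole is underpowered. The matter should be settled before unblinding.

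**What to change.** In the statistical part of the Results section:

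- Name one primary analysis: a mixed model for repeated measures on ln(CRP) at the three post-baseline visits, with ln(baseline CRP) as covariate, visit, group × visit and unstructured covariance.
- Test the group effect jointly over the three visits, and report the geometric mean ratio (experimental/control) with 95% CI at each visit.
- Remove the normality and sphericity tests as the switch between primary methods.
- Drop Friedman for the group comparison.
- Keep the mg/L analysis as a sensitivity analysis.

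The cost is analysis wording only, with no new data. Results will read as percentage differences rather than mg/L, and a rule is needed for values below the assay limit.

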Missing data will be addressed using linear regression models to examine the dose-response relationship, including participants who did not reach the ≥75% adherence threshold as well as those who withdrew from the intervention due to comorbidities or frailty. These individuals will be retained in the analysis to reflect real-world variability.

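### LMM and GEE are offered as interchangeable fallbacks that both handle missing data, but unweighted GEE needs a stronger missingness assumption; one LMM should be pre-specified for CRP and WOMAC

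*Protocol article*

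**What the plan says.** The Results section of the Protocol article states that CRP (four visits) and WOMAC (three visits) "will be analyzed using two-way repeated-measures ANOVA (group × time interaction), contingent upon assumptions of normality and sphericity". If those assumptions fail, "linear mixed models (LMM) or generalized estimating equations (GEE) will be employed as more robust alternatives", and one shared clause calls both "capable of handling missing data and irregular intervals". The article names no order of preference between them and no missingness assumption.

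Other places bear on who will have missing values:

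- **Enrollment:** patients with unexpected medical complications (infection, cardiac or respiratory events) are to stop the programme and leave the study. Patients who miss telerehabilitation sessions or do not answer messages are excluded.
- **Sample size:** "Accounting for a 10% potential attrition rate", 78 becomes 86.
- **Results, last paragraph:** a separate missing-data statement uses linear regression on dose-response. It keeps in the analysis "those who withdrew from the intervention due to comorbidities or frailty".

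**The concern.** A likelihood-based LMM fitted to all visits gives valid estimates when the chance of a value being missing depends on values already observed. Ordinary unweighted GEE in general needs missingness unrelated to the outcome, or dependent only on covariates in the model, here arm and visit. Crediting both with the same property is therefore a wrong statement and not merely a missing detail.

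The article's own text makes the stronger assumption hard to defend. It says that infection raises CRP (Primary outcome) and that high preoperative CRP predicts postoperative infection (Discussion), so observed CRP is linked to events that can remove a patient. The telerehabilitation rule acts mainly on the experimental arm, because controls receive only a booklet, so loss may differ by arm.

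The fallback may well be used. The article expects CRP to peak on the third postoperative day, and such a peak makes unequal variances, and so failed sphericity, plausible. With two unranked models, the choice could also be made after both p-values are known. Blinding the analyst does not prevent this, since a p-value can be read without knowing which arm is which.

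**Working it through.** **Inputs from the article.** "The sample size was estimated using repeated measures analysis of variance with four time points" and two groups; "Assuming a moderate effect size (f = 0.25), α = 0.05, and 80% power (β = 0.20), 78 participants were required"; "The significance level was set at p < 0.05"; 1:1 allocation; a cited CRP difference of 9.12 mg/L with pooled SD 10.95 mg/L.

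**The plan's own figures.** 78 × 1.10 = 85.8, which rounds to 86, so about 43 per arm enrolled and 78 / 2 = 39 per arm evaluable. (78 / 0.9 = 86.7 would give 87; the difference is immaterial here.) The 78 cannot be rebuilt from the stated inputs alone, because the correlation among visits is not given. This point needs only the 39 to 43 patients per arm.

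**Assumptions not in the documents.** No true effect; within-patient correlation ρ = 0.5 (range 0.3 to 0.7); the dropout mechanisms below.

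**Step 1. Bias of GEE with an independence working correlation.** With a separate mean for each arm and visit, this estimator is the plain average of the observed values. If dropout depends on an earlier value z (in SD units), then

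bias of an arm mean = ρ × SD × E[z | observed],

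and the bias of the group difference is the difference of these between arms.

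*Mechanism A:* dropout after baseline driven by baseline CRP, logit slope 1.5 per SD. E[z | observed] is -0.065, -0.122, -0.175 and -0.227 at 5%, 10%, 15% and 20% dropout.

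*Mechanism B:* experimental patients in the top quarter of day-3 CRP miss day 30 with probability q; controls miss 10% at random. The mean of z in the top quarter is 1.271, so E[z | observed] = -0.25q × 1.271 / (1 - 0.25q). This is -0.1271 / 0.90 = -0.141 at q = 0.4 and -0.2542 / 0.80 = -0.318 at q = 0.8.

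| Scenario | Difference in E[z] | ρ = 0.3 | ρ = 0.5 | ρ = 0.7 |
|---|---|---|---|---|
| A, 10% vs 10% | 0 | 0 | 0 | 0 |
| A, 5% vs 15% | -0.110 | -0.03 SD | -0.06 SD | -0.08 SD |
| A, 0% vs 20% | -0.227 | -0.07 SD | -0.11 SD | -0.16 SD |
| B, q = 0.4 | -0.141 | -0.04 SD | -0.07 SD | -0.10 SD |
| B, q = 0.8 | -0.318 | -0.10 SD | -0.16 SD | -0.22 SD |

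With higher loss in the experimental arm, the negative sign favours that arm.

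Simulation with 86 patients agrees (3,000 runs per main scenario of A; 1,500 for the other values of ρ):

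- **GEE, independence:** A at 5% vs 15% gave -0.56 mg/L with normal data and -0.47 with lognormal data. A at 0% vs 20% gave -1.29 mg/L, with -0.73 at ρ = 0.3 and -1.80 at ρ = 0.7. The largest is 1.80 / 9.12 = 20% of the cited difference.
- **GEE, exchangeable:** at most 0.13 mg/L (about 0.01 SD) under A; 0.03 to 0.06 SD under B.
- **Likelihood-based estimation on all visits:** below 0.01 SD under both.

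**Step 2. Type I error if the sandwich variance is uncorrected.** With complete normal data and n per arm, the uncorrected sandwich divides by n instead of n - 1. The 3-df Wald statistic is therefore W = [n / (n - 1)] × T², where T² is Hotelling's statistic with ν = 2n - 2. Hence

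P(W > 7.815) = P(F(3, ν - 2) > 7.815 × (n - 1)/n × (ν - 2)/(3ν)).

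- n = 39: 7.815 × 38/39 × 74/228 = 2.471, giving 6.8%.
- n = 43: 7.815 × 42/43 × 82/252 = 2.484, giving 6.7%.

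Simulation at N = 78 gave 6.9%, against 5.7% with the Mancl-DeRouen correction and 5.3% for the LMM. With lognormal complete data the uncorrected test gave 5.9%. Across the dropout runs the uncorrected standard error was about 1 to 5% too small.

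**The case against.** A reader might infer that health-related dropout does bias the primary result and that the standard errors are too small. The documents do not support either statement. Repeated-measures ANOVA comes first, GEE is one of two fallbacks, and material bias needed both unequal dropout and working independence. The article names neither a working correlation nor a variance estimator, and an article may leave both to the full protocol or analysis plan. So the type I error figure holds only if no correction is used, and even then the excess is modest.

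Three further objections stand.

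- The Enrollment rules mostly concern the prehabilitation phase, before any day-3 value exists. Mechanism B is therefore an assumption about later loss, not something the article describes; mechanism A fits its rules better.
- The last paragraph of Results is about patients who leave the intervention and are kept in the analysis. It does not say that their CRP will be missing.
- An LMM is no cure if a patient is lost because of a CRP rise that was never measured.

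It can also be argued that the wording only contrasts both models with ANOVA, since each can use an incomplete patient's available visits. That is true as far as it goes. It does not tell the analyst that the two then rest on different assumptions, and the open choice remains.

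**Conclusion.** The point holds as a conditional one. The article presents LMM and GEE as equivalent for missing data on the primary outcome and leaves the choice open. They are not equivalent, and its own withdrawal and exclusion rules make the stronger GEE assumption doubtful.

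If GEE is chosen, the group difference can be biased by roughly 0.04 to 0.2 SD, about 0.4 to 2.2 mg/L at SD 10.95. This rests on the assumed correlations, arm-differential dropout and working independence. The bias is near zero with equal dropout and 0 to 0.06 SD with an exchangeable structure. An uncorrected sandwich variance would add a type I error of about 6-7% with normal data. These sizes are modest beside the 9.12 mg/L cited, but the problem is avoidable at little cost.

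**What to change.** Pre-specify one model for CRP (log-transformed) and WOMAC: an LMM with arm, visit and their interaction, using all randomised patients and every available visit, with unstructured covariance, REML and Satterthwaite or Kenward-Roger degrees of freedom. State the missing-at-random assumption. Use this model in place of both the repeated-measures ANOVA and the choice between LMM and GEE. Removing GEE alone would not be enough: the ANOVA in its standard form drops incomplete patients and is exposed to the same dropout, and the trigger for leaving it has nothing to do with missing data.

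If GEE is kept, make it a sensitivity analysis with a small-sample-corrected variance, and state that it needs missingness unrelated to the outcome.

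The cost is a rewrite of the primary-analysis text, with no new data. CRP effects would be reported as ratios instead of mg/L. The LMM relies on its distributional and covariance assumptions; the log scale and unstructured covariance make these more reasonable. It does not remove bias if dropout depends on unobserved CRP, and the plan should say so.

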## Discussion

The primary objective of this trial is to compare the effects of an eight-week semi-supervised home-based prehabilitation program with a control group on biomarkers in patients undergoing TKA. Secondary objectives include evaluating hospital outcomes (length of stay, complications, and readmission rates) and self-reported measures such as function, pain, stiffness, and satisfaction with surgery. We hypothesize that prehabilitation will lead to better outcomes, as prior studies show that exercises improve preoperative health, enhancing surgical recovery.

While postoperative rehabilitation is well-established, patients often undergo surgery in a debilitated state owing to sedentary lifestyles, which correlates with higher complication rates and worse clinical outcomes [6]. Home-based exercise programs are effective in increasing adherence among older adults and, when implemented preoperatively, can improve function, reduce pain and stiffness, lower surgical anxiety and incidence of complications, shorten hospitalization, and improve TKA satisfaction [7].

The day before surgery and the early postoperative period are critical phases of both surgical preparation and recovery. Preoperatively, biomarkers provide key insights into systemic inflammation, nutritional status, and thromboembolic risk, aiding surgical risk stratification and complication prediction. For instance, elevated preoperative CRP levels are an independent predictor of postoperative infection in arthroplasty patients [29]. Increased CRP and IL-6 levels indicate chronic inflammation, while reduced albumin and prealbumin levels suggest poor nutritional status, potentially impairing wound healing [30]. In the early postoperative phase, biomarkers reflect tissue injury, inflammation, and the progression of recovery. CRP levels peak around the third day post-surgery, indicating the magnitude of surgical trauma [17], while IL-6 levels rise earlier, marking the acute inflammatory response [20]. Lactate levels can reveal metabolic stress and inadequate perfusion [23], while IGF-1 plays a critical role in muscle regeneration [21]. Additionally, monitoring D-dimer and fibrinogen levels is crucial for assessing thromboembolic risk [31], while the presence of myokines, such as irisin and lubricin, suggests metabolic and joint-protective adaptations [22]. Finally, hemoglobin and hematocrit levels assist in identifying anemia, and coagulation markers [32] help assess thromboembolic risk.

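### One of the fallbacks named for the primary repeated measures, the Friedman test, has no group term and cannot test prehabilitation; the plan does not say when it replaces the mixed model or GEE

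*Protocol article*

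**What the plan says.** All of the following is in the protocol article. The Discussion gives the primary objective as a between-arm one: to "compare the effects of an eight-week semi-supervised home-based prehabilitation program with a control group on biomarkers in patients undergoing TKA".

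The second paragraph of the Results section covers two outcomes only, CRP at four time points and WOMAC at three. It says these "will be analyzed using two-way repeated-measures ANOVA (group × time interaction), contingent upon assumptions of normality and sphericity". The normality check comes from the paragraph before: "Data normality will be assessed using the Shapiro-Wilk test".

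Two fallbacks follow in the same paragraph:

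- "If these assumptions are violated, linear mixed models (LMM) or generalized estimating equations (GEE) will be employed as more robust alternatives".
- "For non-parametric repeated measures, the Friedman test will be used, followed by Dunn-Bonferroni post-hoc tests when applicable".

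The second names no outcome and no trigger of its own. Secondary outcomes start in the next paragraph, with their own tests.

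**The concern.** The trial asks whether prehabilitation changes CRP relative to control. That is a group or group × time question, and the planned ANOVA, the mixed model and GEE can all address it. Friedman cannot. It ranks each patient's own values over time and asks whether the time points differ. Dunn comparisons after it set time points against each other, not arms.

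The Friedman sentence closes the paragraph on the primary outcome. Elsewhere in Results, methods are also split by normality (t-test or Mann-Whitney, repeated measures correlation or GLMM). An analyst could therefore reasonably read it as the non-normal branch for CRP. The result could be a very small primary p-value that reflects surgery alone, or two per-arm p-values that tempt the reader to compare significance across arms.

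**Working it through.** **1. The routes set side by side.**

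| Method named in Results | Condition stated | Can carry group × time? |
|---|---|---|
| Two-way repeated-measures ANOVA | normality and sphericity hold | yes |
| LMM or GEE | either assumption violated | yes |
| Friedman, then Dunn-Bonferroni | non-parametric repeated measures, when applicable | no |

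Rows 2 and 3 overlap whenever CRP is non-normal, and the text does not say which then applies.

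**2. What the Friedman statistic measures.** With n patients and k time points, ranks are assigned within each patient, and

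Q = [12n / (k(k+1))] × Σ (mean rank at time j − (k+1)/2)².

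No group label enters. Swapping any patients between arms leaves Q unchanged.

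Take n = 78 (the article's requirement before attrition) and k = 4. The article expects a surgical peak in these data: "The third postoperative day (t5) was selected to capture the peak inflammatory response following surgery". Suppose day 3 is every patient's highest value (rank 4) and the other three times do not differ (mean rank 2 each). Then

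Q = (12 × 78 / 20) × [(4 − 2.5)² + 3 × (2 − 2.5)²] = 46.8 × (2.25 + 0.75) = 140.4,

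against a 5% critical value of 7.81 on 3 degrees of freedom. The value is 140.4 whether or not the arms differ in the size of the CRP values. In a single arm (n = 39) it is half that, 70.2, so both arms would be significant.

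**3. Simulation.** The article gives 78 participants and 1:1 allocation, hence 39 per arm. The CRP medians, spread, correlation and effect are assumptions. CRP was log-normal with log-SD 0.8 and correlation 0.5, with 2000 runs per row.

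| Assumed medians (mg/L) | Intervention effect | Pooled Friedman rejects | Friedman significant in both arms | Group × time F test on log CRP rejects |
|---|---|---|---|---|
| 4, 4, 120, 12 | none | 100% | 100% | 5.1% |
| 4, 4, 120, 12 | −0.5 log units from second time point | 100% | 100% | 82% |
| 4, 4, 8, 4.5 | none | 100% | 99.6% | 5.3% |
| equal at all times | none | 4.5% | 0.15% | 5.5% |

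The last row shows that Friedman holds its level for the hypothesis it does test, no change over time. In that row it was significant in exactly one arm in 9.7% of runs, with no difference between the arms.

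**4. Sensitivity to the assumptions.** A second set used medians of 4, 4, 110 and 8 mg/L, log-SDs of 0.9/0.9/0.5/0.9 or 0.6/0.6/0.4/0.6, and correlations of 0.2, 0.4 and 0.6, with no intervention effect. In all six settings pooled Friedman rejected in 100% of trials, and the group × time test on log CRP in 5–6%.

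**5. How likely a fallback is.** In those six settings Shapiro-Wilk failed in at least one arm-by-time cell in 100% of trials. For a single sample of 39 with log-SD 0.8 it failed in about 99%. If CRP is skewed in this way, the ANOVA would rarely be reached.

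**The case against.** A reader might infer that Friedman is the plan's only answer to non-normal CRP, so that a failed normality check would commit the trial to testing surgery instead of prehabilitation. The text does not support that. The first fallback, tied expressly to violated normality or sphericity, is LMM or GEE, and both can carry the group × time contrast. An analyst who follows that sentence still tests the intervention.

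Other points on that side have weight:

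- **Scope.** The Friedman sentence does not name CRP. It might be meant for within-arm time courses, or for the additional blood biomarkers, for which Results names no other repeated-measures test. But it stands in a paragraph that names only CRP and WOMAC, and nothing confines it to another use.
- **The simulations.** A time effect is built in by assuming a surgical peak, and Shapiro-Wilk failures follow from assuming log-normal data. The plan does not say whether raw values or residuals are tested. The only CRP spread in the article, a pooled SD of 10.95 in the Sample size section, has no stated time point. A median of 110 with log-SD 0.5 implies a day-3 SD of about 66 mg/L. So the rates illustrate the point. That Friedman has no group term needs no simulation.
- **LMM versus GEE.** A rule for choosing between these two may sit in an analysis plan that is not shown, and it is not counted here. The Blinding section says that the analyst is blinded to allocation, which limits deliberate choice of method. Neither fact gives Friedman a group term.

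**Conclusion.** The point stands in limited form. The article names competing fallbacks for the primary repeated measures, does not say when Friedman displaces LMM or GEE, and Friedman cannot answer the between-arm objective. That last fact follows from the definition of the test and rests on no assumed CRP values.

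If that route were taken on the pooled sample, the primary p-value would be driven by surgery: 100% rejection with no intervention effect in every setting tried that had a surgical peak, down to an assumed peak of 8 mg/L. Taken per arm, it gives no between-arm comparison. That a fallback will be needed is likely but rests on the assumption of skewed, roughly log-normal CRP. Which fallback would then be used cannot be determined from the text.

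**What to change.** - **Friedman and Dunn.** Delete them for every between-arm question, or state that they only describe time courses within an arm.
- **Primary model.** Pre-specify one model that keeps the group × time contrast whatever Shapiro-Wilk shows. An example is a linear mixed model on log CRP with group, time and group × time, reported as geometric mean ratios with 95% confidence intervals.
- **Baseline.** Use either all four time points as the response, or the three later time points adjusted for baseline log CRP. Baseline should not be both response and covariate.
- **Rank-based check.** If one is wanted, compare the arms at a time point, for example Mann-Whitney or rank ANCOVA on day-3 CRP, and label it as sensitivity only.

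The cost is a change of wording before analysis, with no change to sample size, visits or assays. The downside is that results are expressed as ratios instead of differences in mg/L, which some clinical readers will find less familiar.
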